**Results:**

The primary outcome under evaluation will be the incidence of poststroke epilepsy in the 3 groups following the 18-month study period. Secondary outcomes will encompass the time to the occurrence of the first seizure, the severity of seizures, any treatment-related adverse events, and the modified Rankin scale score at 3 and 18 months. Exploratory outcomes will involve comparing the effectiveness and safety of PER and LEV.

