### Outcome Measures

#### Primary Outcome

The primary outcome measure will be the incidence of poststroke epilepsy and seizure severity at the end of the study period. Univariate ANOVA of the LEV, PER, and placebo groups will be performed. Intention-to-treat analysis will be performed. Participants will be followed up 1, 3, 6, 9, 12, and 18 months after stroke. If a seizure occurs during the prophylactic medication administration period, individual unblinding and adjustment of AEDs will be implemented. If a seizure occurs after the prophylactic medication administration period, ordinary medical care will be provided. We will record seizure type and duration after stroke onset at seizure occurrence **(**Table 1 and Figure 2).

**Table 1 table1:** Summary of follow-up visits.

Visiting time	Within 3 days	3 months	6/9/12 months	18 months
NIHSS^a^	✓			
mRs^b^	✓			✓
MRI^c^	✓			
EEG^d^	✓			
Start of medication	✓			
TEAE^e^	✓	✓		
Occurrence of seizure	✓	✓	✓	✓
Occurrence of death	✓	✓	✓	✓

^a^NIHSS: National Institute of Health Stroke Scale.

^b^mRs: modified Rankin scale.

^c^MRI: magnetic resonance imaging.

^d^EEG: electroencephalograph.

^e^TEAE: treatment-emergent adverse event.

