#### Secondary Outcomes

The secondary outcomes will include the duration until the occurrence of the first seizure, the severity of seizures, the safety and tolerance of the medication, and the overall stroke outcome. During the 18-month follow-up, we will record mortality, medication safety, and tolerability data at each visit. Stroke outcome will be measured using the modified Rankin scale at 3 and 18 months (Table 1 and Figure 2).

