### Statistical Analysis

Continuous variables will be assessed using a 2-tailed *t* test or ANOVA, followed by the Fisher least significant difference test. When data are not normally distributed, analyses will be performed using the nonparametric ANOVA Kruskal-Wallis H test followed by Dunn multiple comparison test for nonrepeated measures and the Friedman test for repeated measures. ANOVA will be used where sessions or quadrants will be treated as a within-subject factor and groups as a between-subjects factor. Analyses will be performed using a chi-square test, Yates chi-square test, or Fisher exact test for nominal variables. Differences will be considered statistically significant at a *P* value <.05, and actual *P* value will be reported, unless *P*<.001.

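### The test named for the primary outcome conflicts with the rule for nominal variables, and no listed method handles censored time to first seizure

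*Protocol article*

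**What the plan says.** - **Primary outcome (Outcome Measures, Primary Outcome).** "The primary outcome measure will be the incidence of poststroke epilepsy and seizure severity at the end of the study period". The next sentence is "Univariate ANOVA of the LEV, PER, and placebo groups will be performed". It does not say whether the ANOVA is for incidence, severity or both. The section also commits to intention-to-treat analysis.
- **Abstract, Results.** "The primary outcome under evaluation will be the incidence of poststroke epilepsy in the 3 groups following the 18-month study period". Here severity is secondary, so the main endpoint is a yes/no variable.
- **Statistical Analysis, nominal variables.** "Analyses will be performed using a chi-square test, Yates chi-square test, or Fisher exact test for nominal variables". No rule is given for choosing among the three.
- **Statistical Analysis, other variables.** "Continuous variables will be assessed using a 2-tailed" t test or ANOVA, followed by Fisher least significant difference. Non-normal data go to the "nonparametric ANOVA Kruskal-Wallis H test followed by Dunn multiple comparison test for nonrepeated measures", or to Friedman for repeated measures.
- **Statistical Analysis, repeated measures.** "ANOVA will be used where sessions or quadrants will be treated as a within-subject factor and groups as a between-subjects factor".
- **Secondary Outcomes.** These include "the duration until the occurrence of the first seizure". Mortality is recorded at each visit, and Table 1 lists the occurrence of death by visit. No section gives death a role in the analysis.

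**The concern.** There are two separate problems.

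First, incidence has two test assignments. ANOVA is the only test named beside the primary outcome, and the general rule for nominal variables points to chi-square or Fisher. A primary endpoint should have one named test before the final analysis.

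Second, time to first seizure is a duration that most patients will not have. The listed methods (t test, ANOVA, Kruskal-Wallis, Friedman, chi-square and Fisher) contain no survival method. To apply any of the duration tests, the analyst must invent a value for patients who stay seizure-free, die or are lost, or else leave them out. Leaving them out compares groups selected on the outcome. Using death time as the event time mixes mortality with seizures. The result would then depend on a coding choice made outside the stated plan.

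The sentence on sessions and quadrants corresponds to nothing described in this trial, which suggests that the methods text was not fitted to the design.

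**Working it through.** The article gives no figure of its own on this point, so there is none to reproduce first.

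**Inputs from the article:** 180 patients and 3 groups of equal size (60 per arm); 18 months of follow-up; alpha .05; late-seizure risk of 7%-18% (Introduction, Background), used here as a range for the placebo risk. **Assumptions:** a drug effect that halves the placebo risk; constant hazards; 18-month mortality of 20% in every arm, or 15/30/30% (placebo/drug/drug). The article gives no death rate.

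**Step 1: does ANOVA on 0/1 data mislead?** Let N be the number of patients, k the number of groups and X² the Pearson chi-square. For 0/1 data, SSB/SST = X²/N, so

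F = [(N − k)/(k − 1)] × X²/(N − X²).

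F rises steadily with X², so only the cut-offs can differ. With N = 180 and k = 3, the chi-square cut-off of 5.991 becomes F = 88.5 × 5.991/174.009 = 3.047. The ANOVA cut-off, F(2, 177), is 88.5 × (0.05^(−2/177) − 1) = 3.047. In 200,000 simulated trials per scenario the two tests never disagreed:

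| Risk, placebo/LEV/PER | Rejections, ANOVA | Rejections, chi-square |
|---|---|---|
| equal at 7%, 12% or 18% | 4.7%-5.2% | 4.7%-5.2% |
| 18/9/9% | 32.5% | 32.5% |
| 12/6/6% | 21.0% | 21.0% |
| 7/3.5/3.5% | 12.5% | 12.5% |

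**Step 2: how many patients have no seizure time?** 1 − 0.18 = 82% and 1 − 0.07 = 93% of untreated patients, before any death or loss.

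**Step 3: how much does the coding of time to first seizure matter?** Simulation with 60 per arm, three-group tests and exponential seizure and death times; log-rank censors at death and at 18 months.

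| Analysis | Power, 18/9/9%, deaths 20% in each arm | False positives, no seizure effect, deaths 15/30/30% |
|---|---|---|
| Log-rank, censored | 28% | 5% |
| Kruskal-Wallis, seizure-free set to 18 months | 27%-28% | 5% |
| Kruskal-Wallis, patients with seizures only | 4% | 5% |
| Kruskal-Wallis, death time as event time | 13% | 27%-31% |

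Ranges show the spread across separate simulation runs. With a larger effect (18/6/6%, deaths 20% in each arm), the power figures in the same order are 54%, 54%, 3% and 20%. A two-arm version without deaths shows the same for the t test: 5% among patients with seizures against 26% for log-rank, but about 21% if seizure-free patients are set to 18 months.

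**Step 4: do unequal deaths distort raw incidence?** With seizure hazard s = −ln(0.82)/18 and death hazard d = −ln(1 − mortality)/18, the observed 18-month incidence is [s/(s + d)] × [1 − exp(−18(s + d))].

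- Mortality 15%: (0.1985/0.3610) × (1 − 0.697) = 16.7%.
- Mortality 30%: (0.1985/0.5551) × (1 − 0.574) = 15.2%.

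The gap is 1.5 points, or about 0.9 patients in an arm of 60. A chi-square test on raw incidence in this setting rejects in 4.5%-5.6% of trials, so there is no material inflation.

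**The case against.** **The primary analysis is not harmed.** A reader might infer that ANOVA on a yes/no outcome makes the primary analysis wrong or powerless. Step 1 shows otherwise. The low power comes from 60 per arm with few events, which is a separate matter. The ANOVA sentence may also be meant for severity, which sits in the same outcome definition. This objection stands; what remains is a conflict of wording.

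**The harm to time to first seizure depends on coding.** One might conclude that an effective drug must show no effect under the stated methods. That follows only if seizure-free patients are dropped. The article does not say so, and its intention-to-treat commitment points the other way. Setting seizure-free patients to 18 months performs like log-rank. This stands, and it limits the criticism to the unstated coding.

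**Deaths and raw incidence.** A reader might claim that higher mortality on active drug alone creates a seizure benefit that a competing-risk analysis would remove. The 15% and 30% figures are assumptions, and the formula in step 4 is the same cumulative incidence that an Aalen-Johansen estimate would report. That estimate would show the same 16.7% and 15.2%. Only a comparison of cause-specific hazards removes the gap.

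**The omnibus test.** It includes PER versus LEV, which the abstract calls exploratory, but replacing it with two Holm-adjusted contrasts against placebo changes power only from 33% to 34%. The article does not need this change.

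**Scope.** The article is condensed and the analysis plan is not shown, so censoring rules may exist elsewhere. Time to first seizure is also secondary, and its place under t test, ANOVA or Kruskal-Wallis is inferred from the list. This is a fair limit. But the article does not simply defer its methods: it sets out a list, and nothing on that list handles a censored duration.

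**Conclusion.** The concern holds in limited form, as something that should be fixed. The Primary Outcome and Statistical Analysis sections give incidence two different tests and must be reconciled; the choice would not change the decision at this sample size. The listed methods do not suit time to first seizure. Depending on coding that the article does not state, they range from equivalent to log-rank, through almost no power (about 4% against 28%), to 27%-31% false positives.

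The power figures assume an 18% placebo risk, a halving by both drugs, constant hazards and 20% mortality. The false-positive figure assumes mortality of 15/30/30%. The document supplies only the 18%, as the upper end of a background range. The 82%-93% without an event follows directly from the article's own risk range.

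**What to change.** 1. Name one test for incidence, chi-square or Fisher, with the rule for choosing between them. Report risk differences of LEV and PER against placebo with confidence intervals.
2. State that ANOVA or Kruskal-Wallis applies to seizure severity only.
3. Delete the sentence on sessions and quadrants.
4. Analyse time to first seizure by Kaplan-Meier and log-rank, or by a cause-specific Cox model, censoring at last contact and at death. Add cumulative incidence with death as a competing event, and report mortality by arm.

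The cost is analysis wording. The article already records the time of a seizure after stroke onset. For death, Table 1 shows only occurrence by visit, so the sponsor should confirm that dates of death are recorded. Recruitment began in 2020, follow-up was ongoing at publication, and unblinding is planned at 3 months, so the wording should be fixed and dated before the final 18-month analysis.

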### Intervention

The participants will be divided into 3 groups: the control (placebo) group and the 2 experimental groups (LEV and PER). The patients, investigator, study assessors, and data analysts will remain blind to the treatment assignments from the time of randomization. Because we will conduct block randomization for group allocation, we anticipate that the percentage of patients receiving tissue plasminogen activator or intravenous thrombectomy will be similar in the 3 groups.

The major MCA infarctions typically require the early implantation of a nasogastric tube, and to account for the design of blinding, preventive drugs will be administered in powdered form. The study team works with pharmacists to ensure that medications for the experimental and control groups have similar color, fragrance, and taste. After being ground up, the drugs are packaged in identical medication bags, and a reminder label is affixed to the outer packaging to remind patients to take their medication regularly and for the appropriate duration.

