The three groups are described as follows, and the study flowchart is shown in Figure 1: (1) For the control group, a placebo will be administered to patients, and we will maintain standard stroke care during hospital admission if no acute seizure occurs during this period. If an acute seizure occurs, unblinding will be performed, and we will administer AEDs not including LEV or PER; the patient will be maintained on these AEDs. (2) For the LEV group, we will prophylactically administer 1000 mg of LEV per day to patients from the first day of admission in addition to standard stroke treatment. The LEV treatment duration will be 3 months. (3) For the PER group, we will prophylactically administer 4 mg of PER per day to patients from the first day of admission in addition to standard stroke treatment. The PER treatment duration will be 3 months. (4) After the patient is discharged from the hospital, their respective medication will be administered orally for up to 3 months. (5) All patients will receive follow-up for 18 months, and the incidence of late-onset epilepsy will be documented. Seizure characteristics, including semiology, frequency, and severity, will be analyzed in the 3 groups. The relationship of seizure semiology to stroke-related localization will be verified. (6) For those who have acute seizures during hospital admission, unblinding will be performed, and either LEV or PER will be administered for treatment according to their group. The dosage will be adjusted according to real clinical needs. These patients will be treated as having epilepsy based on the 2016 definition of epilepsy [41] and be maintained on LEV or PER after hospital admission. The administration of LEV or PER to patients with acute seizures will still be considered prophylactic therapy because patients with acute seizures have a considerably higher risk of developing poststroke epilepsy. (7) Because up to 20% of patients with anterior circulation ischemic stroke may experience electrographic seizures during the acute stage of stroke without clinically overt seizures [42], we will arrange 1 routine electroencephalogram (EEG) at the acute stage for each patient. Prophylactic AED therapy will be administered according to the group the patient is allocated to if any electrographic seizure, including periodic lateralized epileptiform discharge (PLED), is identified in the EEG. (8) Unblinding will be implemented at 3 months, and the final analysis will be conducted at 18 months.

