### Randomization and Blinding

Block randomization of eligible participants will be performed to form the LEV, PER, and placebo groups. Blinding of participants, clinicians, and data collectors will be performed so that these individuals do not have access to group assignment details (Figure 2). Before accepting the case, the pharmacist, who is a nonresearch team member, sets the blocks and determines the distribution of random numbers using a random number table. The pharmacist is responsible for conducting all phases of the research. Additionally, the 3 topic groups can be equally distributed among participants through random assignment.

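### A seizure during dosing breaks the blind that the article promises for everyone, and the text does not protect the later judgement of seizure type, severity and epilepsy status

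*Protocol article*

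**What the plan says.** The article makes two blinding statements. Intervention: "The patients, investigator, study assessors, and data analysts will remain blind to the treatment assignments from the time of randomization". Randomization and Blinding: "Blinding of participants, clinicians, and data collectors will be performed so that these individuals do not have access to group assignment details". Neither names an exception.

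Three rules open the code when a seizure occurs:

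- Primary Outcome, for any seizure while study drug is given: "If a seizure occurs during the prophylactic medication administration period, individual unblinding and adjustment of AEDs will be implemented".
- Intervention, item 1, control group: "If an acute seizure occurs, unblinding will be performed, and we will administer AEDs not including LEV or PER".
- Intervention, item 6, active groups: "For those who have acute seizures during hospital admission, unblinding will be performed, and either LEV or PER will be administered for treatment", according to the allocated group.

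Item 6 adds a classification rule: "These patients will be treated as having epilepsy based on the 2016 definition of epilepsy". Item 1 does not repeat it for controls.

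Incidence of poststroke epilepsy and seizure severity together form the primary outcome. Time to first seizure, and severity again, are secondary outcomes. Seizure type and time since stroke are recorded when the seizure occurs. The article does not say who records them or whether that person knows the arm.

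**The concern.** A code break for a patient's care is ordinary. Here, however, the trigger is the outcome event, so arm knowledge can enter only the records of patients with events, and those records make up the primary and severity outcomes. If the person who grades the seizure or decides whether it counts as epilepsy knows the arm, doubtful cases can be read differently in placebo and active patients. That can create a drug effect or hide one.

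The treatment after the code break adds a second route. Controls move to drugs other than LEV and PER, while active patients stay on LEV or PER. A rater who reads the chart can infer the arm without being given the code.

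**Working it through.** **1. The rules side by side**

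| Rule | Who or when | Exception or limit stated |
|---|---|---|
| Intervention, blinding sentence | Patients, investigator, assessors, analysts blind from randomization | None |
| Randomization and Blinding | Participants, clinicians, data collectors have no access to assignment | None |
| Intervention, item 1 | Control patient with an acute seizure: code broken, drugs other than LEV or PER | Recipient of the code not named |
| Intervention, item 6 | Active patient with an acute seizure: code broken, LEV or PER by group | Recipient of the code not named |
| Primary Outcome | Any seizure during dosing: individual code break, drugs adjusted | Recipient of the code not named |

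The first two rows cannot hold together with the last three. Treatment cannot be chosen by arm while clinicians have no access to the assignment. The text does not say which of the other blinded roles remain blind.

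**2. Which outcome components are exposed**

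A first seizure is noticed before its own code break, so its occurrence and date can be captured blind. Exposed are the components that may be settled afterwards: seizure type, severity, epilepsy status and any later seizure in the same patient.

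**3. How many patients**

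Inputs: N = 180 (Methods, Overview); early seizures 2.4%-5.4% and late seizures 7%-18% (Background). Assumption: these general stroke rates apply to this trial.

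- Early: 180 × 0.024 = 4.3 and 180 × 0.054 = 9.7, so about 4 to 10 patients.
- Late: 180 × 0.07 = 12.6 and 180 × 0.18 = 32.4, so about 13 to 32 patients.

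Two adjustments pull in opposite directions, and the article gives a figure for neither. Procedure and Assessment uses a baseline EEG to exclude patients with early or concurrent seizures, which lowers the early count. Late seizures that fall within the 12 weeks of dosing also open the code, which raises the number affected.

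**4. Can one event matter?**

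Assume 60 per arm (180 / 3) and, for illustration only, these event counts in two arms. All three tests are listed under Statistical Analysis.

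| Events | Pearson | Yates | Fisher |
|---|---|---|---|
| 11 vs 4 | .053 | .098 | .095 |
| 11 vs 3 | .023 | .047 | .043 |
| 8 vs 3 | .114 | .206 | .204 |
| 8 vs 2 | .048 | .099 | .095 |

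One event judged differently crosses .05 under all three tests in the first pair, but only under the uncorrected test in the second. The table shows that the result can turn on one event; it does not estimate bias.

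**5. A bias scenario and its limits**

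Assume no true effect, the same late risk in both arms (7.5%, 12% or 18%), and that half of the active-arm early events are not counted. The rejection rate of the nominal 5% test, by exact enumeration, is then:

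- Uncorrected chi-square, 5.4% early rate: 7.3%, 6.5%, 6.6% (without the non-counting 4.8%-5.2%).
- Uncorrected chi-square, 2.4% early rate: 5.1%-5.6%.
- Yates, 5.4% early rate: about 3.9%.

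A rate clearly above 5% therefore needs the upper early rate, the uncorrected test and an assumed 50% non-counting. The finding does not rest on it.

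**The case against.** **Blind assessment is already promised.** The two blinding statements cover assessors, data collectors and analysts, and an individual code break is compatible with telling only the treating clinician. This stands in part. A reader might infer that early seizures will be judged with the arm known, or that nothing requires blind judgement. The documents do not support either reading: no sentence gives assessors the code or places grading after the code break. What remains is that the promise has no exception, the unblinding rules contradict it, and no stated mechanism keeps it.

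**Such detail belongs in the full protocol.** Adjudication steps and the order of form entry may well be there, and their absence from an article is no finding. The contradiction between stated rules is one, because clinicians are named as blind in one section and must act on the code in another.

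**The size is small and depends on choices.** This largely stands. The early rates are not specific to this trial, the EEG exclusion may lower them, and the error-rate scenario exceeds 5% only under the conditions shown. Assumed non-counting in the active arms also sits badly with item 6, which treats acute seizures there as epilepsy. That rule raises its own question, because it is not repeated for controls. A reader might infer that acute seizures count only in the active arms. The text does not say so, and the sentence may concern treatment rather than outcome counting, but it should be made explicit.

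**The scheduled unblinding is the larger exposure.** The article also states "Unblinding will be implemented at 3 months, and the final analysis will be conducted at 18 months", and the Discussion puts the peak of late seizures at 6 to 12 months. That is a separate and probably larger matter. Resolving it would not resolve the conflict described here.

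**Conclusion.** The concern holds as a contradiction in the stated rules that bears on the primary outcome. Everyone is said to stay blind, yet the outcome event opens the code and arm-specific treatment follows. As written, type, severity, epilepsy status and later seizures can be judged with the arm known. Occurrence and date of a first seizure are less exposed.

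The size is about 4 to 10 of 180 patients at the Background's early rates, if those rates apply here. It is lower if the EEG exclusion removes some and higher by the unstated number of seizures from week 2 to month 3. That bias will occur, or that the type I error will exceed 5%, cannot be concluded from the article. The change is worth making because event counts are small enough for one judgement to matter and the remedy is cheap.

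**What to change.** 1. Reconcile the sections: state that an event-triggered code break goes only to those who need it for the patient's care, and name this exception in the Intervention and the Randomization and Blinding statements.
2. Have an existing study assessor, who receives neither the code nor the drug choice made after the code break, record from contemporaneous notes whether a seizure occurred, its date, type and severity, and the epilepsy classification. Lock that record.
3. State one rule for whether an acute seizure counts toward poststroke epilepsy, and apply it identically in all three arms.
4. Keep assessors and analysts blind to that patient's arm afterwards, including for later seizures.

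Patient care and the timing of the code break do not change. The cost is a few sentences, one dated form page, and the effort of keeping the code and the post-event drug list from the assessor. The Results section describes follow-up as ongoing, so where contemporaneous notes exist, events that have already occurred could be graded in the same way.
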